**FOOD CONSUMPTION**

Food consumption will be measured at all visits using a short, self-administered questionnaire^51^ recently developed to assess adherence to the Mediterranean diet in the Italian population. In this contest, it will be used to record daily or weekly intake of the main food groups over the previous months and the change over the study (see Appendix E).

**INTERNATIONAL PHYSICAL ACTIVITY QUESTIONNAIRE**

Physical activity will be measured with the IPA Questionnaire (IPAQ) at all visits. This questionnaire consists of questions that record the frequency and duration of mild, moderate, and strenuous exercise performed during free time in the previous 7 days. It measures physical activity and inactivity.

It is a validated self-reported measure of exercise that has been reliably used in previous studies^52^. The total hours per week spent in each activity will be multiplied by the estimated metabolic cost of each activity (metabolic equivalent (MET) value) as determined from the Compendium of Physical Activities^53^ (see appendix).

**BODY COMPOSITION MEASUREMENTS**

Body composition will be assessed at T1, T4 and T6, using bioelectrical impedance vector analysis (BIVA) (Nutrilab device, AKERN Srl – Italy). BIVA is an accurate method for a quick measurement of body compartments^54, 55^. The direct analysis of the two components of the impedance vector (Z), resistance (R, Ohm) and reactance (Xc, Ohm), allows a semiquantitative evaluation of body composition in terms of body cell mass and hydration status. Data for total body water (TBW), body cell mass (BCM), extracellular water (ECW), fat-free mass (FFM), fat mass (FM) and percentage fat mass (% FM) will be available for all participants and will be used for identifying changes of fat and fat-free mass over the study period.

Depending on local availability, in a sub-sample of women, body composition will be quantified via dual-energy X-ray absorptiometry (DEXA) at T1 and T6. DEXA is considered the gold standard for total body composition analysis^56^, but it is a medical exam and not a regularly used for body composition assessment. In this study, DEXA will be used to measure tissue absorption of high- and low-energy X-ray beams that pass through the participant in a supine position. Those measurements provide a multicompartment assessment, including FM, FFM, and bone mineral density. The DEXA device automatically calculates the body composition of each participant.

## 7.4 Evaluation During Study Intervention

A phone contact or tele-consulting will be performed at T2, T3, T5 to motivate and support adherence to ICR, LI, and to monitor tamoxifen toxicity.

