## 1.2 Secondary Objectives

The secondary aims are:

-to verify whether ICR significantly modulates main and secondary endpoints such as HOMA-index, immune and inflammatory markers, lipid profile, Adiponectin/Leptin (A/L) ratio, quality of life (QoL), Body mass index (BMI), fat body composition, safety and toxicity;

-to verify whether LDT significantly modulates secondary endpoints, such as HOMA-index, immune and inflammatory markers, lipid profile, A/L ratio, QoL, BMI, fat body composition, safety and toxicity;

-to investigate differences in microbiome composition by arms and the effect of changes in microbiome on QoL taking into account circulating biomarkers, cytokines, immune modulators and inflammatory proteins in serum;

- to investigate MD (Mammographic Breast Density) changes by LDT vs LI, with or without ICR. This aim will be performed in a subgroup of participants (not all the participants will undergo mammography due to younger age).

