# 3. STUDY DESIGN

The TOLERANT (Low dose **T**am**O**xifen and **L**if**E**style changes for b**R**east c**AN**cer preven**T**ion) study is a randomized four-arm phase II intervention trial that will enroll 200 participants at high risk of breast cancer in four Italian centers (Milan, Genoa, Padua and Naples).

Potentially eligible women will be informed about the study and will provide signed informed consent before participation. At baseline, participants will be screened to confirm eligibility and will be randomly assigned (1:1:1:1) to one of the four intervention arms (Figure 1):

*Arm 1:* Low dose Tamoxifen (LDT) i.e 10 mg every other day;

*Arm 2:* Low dose Tamoxifen (LDT) + Intermittent Caloric Restriction (ICR);

*Arm 3:* Lifestyle intervention (LI) using a step counter;

*Arm 4:* Lifestyle intervention (LI) using a step counter + Intermittent Caloric Restriction (ICR).

Figure 1

[figure not shown]

Stratification: center and disease status (high risk vs previous IEN)

A schematic description of the study procedures is reported in figure 2.

Figure 2

[figure not shown]

Trained staff including dietitians/nutritionists will provide advices based on international and national recommendations (WCRF.2018; CREA, 2019 https://www.crea.gov.it/web/alimenti-e-nutrizione/-/linee-guida-per-una-sana-alimentazione-2018) at baseline to all participants. Depending on intervention allocation, dietitians/nutritionists will provide a caloric restriction plan to Arm 2 and 4. Participants included in Arm 3 and 4, will receive a step counter that encourages both increased physical activity and decreased sedentary time. Depending on intervention allocation, tamoxifen pills will be provided (Arm 1 and 2). All participants will receive a calendar in order to record drug intake, ICR dates and weekly step counter where appropriate. The study interventions will last 6 months.

To maintain high compliance during the 6-month intervention phase (T2, T3 and T5) participants will receive phone calls in order to monitor and reinforce adherence to the proposed intervention, and to record possible adverse effects. At visit T1, T4 and T6 blood samples will be collected, anthropometric measures, study questionnaires will be collected. Stool will be collected at T1 and T6. Depending on local availability, a sub-sample of participants will be invited to do DEXA for adipose tissue evaluation.

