## 5.4 Intervention Modification

Participants will be asked to maintain the assigned intervention throughout the treatment period. In particular, for the tamoxifen arms due to the short time of treatment no dose modification will be applied.

Toxicity will be evaluated using the NCI terminology criteria (CTCAE version 5.0).

If grade 1 or 2 toxicity occurs, the participant will be maintained on treatment irrespective of attribution to the study drug. However, treatment discontinuation should be planned if a persistent/recurrent and intolerable Grade 2 toxicity occurs.

In case of grade 3 toxicity unrelated, unlikely or possibly related to study treatment, participant may remain on treatment as per physician judgment. Women who experience other grade 3 or more severe adverse events will be removed from intervention.

| Toxicity | Attribution to study arm | | | | |
| --- | --- | --- | --- | --- | --- |
| Grade | Unrelated | Unlikely | Possible | Probable | Definite |
| 1 | C | C | C | C | C |
| 2 | C | C | C | C | C |
| 3 | C^1^ | C^1^ | C^1^ | W | W |
| 4 | W | W | W | W | W |

C = Continue intervention; C^1^ = Continue intervention as per physician judgment; W = Intervention withdrawal.

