**SCHEDULE OF EVENTS**

| Evaluation/ Procedure | T0  Screening Visit  Days -30-1 | T1  Baseline Visit/Randomization  Day 0 | T2  Phone call/ teleconsulting  (within 1 month) | T3  Phone call/ teleconsulting  (2 months) | T4  Visit  (3 months) | T5  Phone call/ teleconsulting  (5 months) | T6  Final Visit  (6 months) |
| --- | --- | --- | --- | --- | --- | --- | --- |
| Informed Consent | X |  |  |  |  |  |  |
| Stool Collection kit | X |  |  |  | X |  |  |
| Assess eligibility | X | X |  |  |  |  |  |
| Medical history |  | X |  |  |  |  |  |
| Physical exam/ anthropometric measures and body composition (BIVA) |  | X |  |  | X |  | X |
| Tobacco/alcohol use assessment |  | X |  |  |  |  |  |
| Fasting blood collection^a-b^ |  | X^b^ |  |  | X |  | X^b^ |
| Gravindex |  | X* |  |  |  |  |  |
| Stool collection |  | X |  |  |  |  | X |
| Mammography (according to Institutional guidelines)^c^ |  | X |  |  |  |  | X |
| Body fat composition (DEXA)^d^ |  | X |  |  |  |  | X |
| Concomitant medications |  | X |  |  | X |  | X |
| Baseline Symptoms |  | X |  |  |  |  |  |
| Randomization |  | X |  |  |  |  |  |
| Nutrition counseling |  | Arms 2, 4 only | Arms 2, 4 only | Arms 2, 4 only | Arms 2, 4 only | Arms 2, 4 only |  |
| Physical activity counseling |  | Arms 3, 4 only | Arms 3, 4 only | Arms 3, 4 only | Arms 3, 4 only | Arms 3, 4 only |  |
| Tamoxifen safety |  |  | Arms 1, 2 only | Arms 1, 2 only | Arms 1, 2 only | Arms 1, 2 only | Arm 1, 2 only |
| WCRF recommendations | X | X |  |  |  |  |  |
| Collect study agent |  |  |  |  |  |  | X |
| Compliance |  |  | X^g^ | X^g^ | X^e^ | X^g^ | X^e^ |
| Review diary |  |  |  |  | X |  | X |
| Adverse events |  |  | X | X | X | X | X |
| Study Questionnaires: QoL, DIET and IPAQ | X^f^ | X |  |  | X |  | X |

* In women of childbearing potential only

a. Glycemia will be measured locally and blood specimen will be collected for biomarkers as per Manual of procedure

b. Additional blood collection in dedicated tubes for RNA extraction as per Manual of procedure.

c. Mammogram will be performed only in a subgroup of participants based on their age and center guideline, and can be within 6 or 12 months from baseline visit depending on disease status.

d. In a subgroup of participants only, depending on local availability.

e. Revision of diary completion only. Unused and/or empty blisters will be returned at month 6 visit arms 1,2

f. 3-day food records only

g. Compliance with Intermittent Caloric Restriction

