## 10.1 Adverse Events

Reportable AEs

All AEs that occur after the informed consent is signed and baseline assessments are completed must be recorded on the AE CRF (paper and/or electronic) whether or not related to study agent.

Cases of overdose, medication error, drug abuse, or drug misuse, along with any associated adverse events, should be reported.

AE Data Elements:

The following data elements are required for adverse event reporting.

- AE verbatim term
- NCI Common Terminology Criteria for Adverse Events version 6.0 (CTCAE v 5.0) AE term (MedDRA lowest level term)
- CTCAE (MedDRA) System Organ Class (SOC)
- Event onset date and event ended date
- Treatment assignment code (TAC) at time of AE onset
- Severity grade
- Attribution to study agent (relatedness)
- Whether or not the event was reported as a serious adverse event (SAE)
- Whether or not the subject dropped due to the event
- Outcome of the event

Severity of AEs

Identify the AE using the CTCAE v 5.0. The CTCAE provides descriptive terminology (MedDRA lowest level term) and a grading scale for each AE listed. A copy of the CTCAE can be found at:

https://ctep.cancer.gov/protocolDevelopment/electronic_applications/docs/CTCAE_v5_Quick_Reference_5x7.pdf

AEs will be assessed according to the grade associated with the CTCAE term. AEs that do not have a corresponding CTCAE term will be assessed according to the general guidelines for grading used in the CTCAE v5.0 as stated below.

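### A tamoxifen-only safety item on top of the common adverse-event collection leaves the LDT versus LI safety comparison open to unequal ascertainment

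*Protocol*

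**What the plan says.** Safety and toxicity is a declared comparison. One of the secondary aims in Protocol section 1.2 is "to verify whether LDT significantly modulates secondary endpoints, such as HOMA-index, immune and inflammatory markers, lipid profile, A/L ratio, QoL, BMI, fat body composition, safety"; section 8.2 likewise names toxicity, alongside safety, as a secondary endpoint.

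The Schedule of Events has two safety rows. The general one carries no arm restriction at T2 to T6: "Adverse events | | | X | X | X | X | X". The other starts "Tamoxifen safety | | | Arms 1, 2 only | Arms 1, 2 only" and continues to T6, always for Arms 1 and 2.

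The text describes the calls at T2, T3 and T5 in two ways. Section 7.4 gives their purpose as "to motivate and support adherence to ICR, LI, and to monitor tamoxifen toxicity". Section 3 says "participants will receive phone calls in order to monitor and reinforce adherence to the proposed intervention, and to record possible adverse effects", without limiting this to any arm.

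Attribution of events has three labels. The data-element list in section 10.1 has "Attribution to study agent (relatedness"), the table in section 5.4 is headed "Attribution to study arm", and later in section 10.1 the event is classified by its relation to the intervention. For serious events, section 10.2 asks for the relation to each specific study treatment.

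**The concern.** Arms 1 and 2 receive a drug, and Arms 3 and 4 a step counter with advice. With no placebo, everyone concerned knows the arm. Many of the events listed for tamoxifen in section 6.2 (hot flushes, sweating, insomnia, dizziness, cramps) are subjective, and whether such a symptom is recorded depends partly on whether and how it is asked about. An extra safety item in the drug arms alone, together with a section that names only tamoxifen toxicity as the safety purpose of the calls, invites closer questioning in those arms.

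The true difference may also be small: section 2.4 says that side effects of low-dose tamoxifen are only marginally above placebo. A modest difference in questioning could be as large as the effect sought, and the tolerability message of the trial draws on this comparison.

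**Working it through.** **The plan's own figure.** No figure is stated for the safety comparison. The only design calculation is for SHBG in section 12.1: 90 per group, difference 15, SD 35, two-sided 5%. Recomputed power is 0.82 with either the normal approximation or the t-test, against 80% stated, and 180 / 0.90 = 200 enrolled. Nothing here changes those figures. For safety, section 12.4 makes all randomised participants evaluable, so 200 at 1:1:1:1 gives 100 in Arms 1 and 2 and 100 in Arms 3 and 4.

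**What each group is asked.**

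| Source of safety information | Arms 1 and 2 | Arms 3 and 4 |
| --- | --- | --- |
| General adverse events (Schedule of Events, T2 to T6) | 5 contacts | 5 contacts |
| Tamoxifen safety item (Schedule of Events, T2 to T6) | 5 contacts | 0 contacts |
| Toxicity assessment at T4 and T6 (Schema) | yes | yes |
| MenQoL, 29 items, at T1, T4 and T6 | yes | yes |

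The number of contacts and the general collection are equal. The tamoxifen item is not: 5 against 0. T2, T3 and T5 are phone or tele contacts, so at those three the extra item can only be questioning.

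**Size, as an illustration only.** The protocol gives neither an event rate nor a capture rate. Assume that true risk is equal in the two groups, that p is the proportion with a given symptom recorded under LDT, and that the LI arms record a fraction s of what the LDT arms record. Then:

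- spurious difference = p − s·p = p(1 − s);
- chance of a nominally significant excess under LDT = Φ[(d − 1.96·SE0) / SE1], where d is that difference, SE0 the standard error with pooled proportions and SE1 the unpooled one, with n = 100 per group.

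Example with p = 0.30 and s = 0.7. The recorded proportions are 0.30 and 0.21, so d = 0.09. The pooled proportion is 0.255.

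- SE0 = √(2 × 0.255 × 0.745 / 100) = 0.0616
- SE1 = √((0.30 × 0.70 + 0.21 × 0.79) / 100) = 0.0613
- (0.09 − 1.96 × 0.0616) / 0.0613 = −0.50, and Φ = 0.31

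| p recorded under LDT | s = 0.9 | s = 0.8 | s = 0.7 |
| --- | --- | --- | --- |
| 0.10 | 1 point, 4% | 2 points, 7% | 3 points, 12% |
| 0.30 | 3 points, 7% | 6 points, 16% | 9 points, 31% |
| 0.50 | 5 points, 11% | 10 points, 29% | 15 points, 57% |

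Each cell gives the spurious difference in percentage points and the chance of a false excess under LDT. The formula counts that direction only, for which the rate with equal capture (s = 1) is 2.5%.

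**The case against.** The strongest reply is that safety collection is already common to all arms. The general adverse-event row covers everyone at the same five contacts. Section 3 has the calls record adverse effects in all participants, the Schema has toxicity assessment at T4 and T6 for all, section 8.2 applies CTCAE v5.0 without arm restriction, and section 10.1 requires every event to be recorded whether or not related. This stands, and it means that a reader who infers that the comparison is biased goes further than the documents allow. Equal contact and equal grading do not guarantee equal questioning, however, so the exposure remains.

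Nor does any section say what the tamoxifen safety item asks. Section 6.2 is a list of reported events, not a questionnaire, and the wording may sit in case report forms that are not shown. One cannot state that those symptoms are prompted in Arms 1 and 2 and left unasked in Arms 3 and 4. MenQoL in fact asks every arm, in the same words, about hot flushes, sweating, sleep, muscle and joint pain and fatigue at T1, T4 and T6. It does not remove the concern: it is a quality-of-life endpoint separate from CTCAE toxicity, it is not given at the calls, and its 29 items include none for dizziness, which is on the section 6.2 list.

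A reader might also infer that harms of ICR and LI go unrecorded. Section 5.1 monitors ICR side effects by phone at months 1, 2 and 5, and section 10.1 monitors intake, dehydration and activity injuries. Nor does the tamoxifen row unbalance the ICR contrast, which sets Arms 2 and 4 against Arms 1 and 3 with one tamoxifen arm on each side.

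The capture fractions above are assumptions. Section 12.1 also plans multiplicity adjustment for the exploratory secondary objectives, so an unadjusted 5% test is not the planned criterion.

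**Conclusion.** The point holds as a risk, not as a demonstrated bias. The Schedule of Events puts a tamoxifen safety item at five contacts in the drug arms and none in the LI arms, and section 7.4 describes the calls more narrowly than section 3. With allocation known, the LDT versus LI safety comparison is open to unequal ascertainment of subjective symptoms, and the likely direction is more events recorded under LDT. The size cannot be derived from the protocol: it is zero if questioning turns out equal, and 3 to 9 points under the assumed 30% recorded incidence and relative capture of 0.9 to 0.7.

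The attribution wording is a smaller, separate matter. It would be tempting to say that the adverse-event form can record attribution only to a drug. That is not supported, because section 10.1 also classifies relation to the intervention and section 10.2 requires attribution to each treatment for serious events. What remains is a mismatch of labels, and no stated requirement to separate tamoxifen from ICR for non-serious events in Arm 2, although section 8.2 singles out safety of the combined intervention. The primary SHBG endpoint and the sample size are unaffected.

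**What to change.** 1. Keep the tamoxifen safety item in Arms 1 and 2 for monitoring. Replacing it could lose drug-specific checks.
2. Add one fixed symptom checklist, built from the tamoxifen events in section 6.2 and the fasting and activity events in section 10.1. Ask it in the same words in all four arms at T1, where baseline symptoms are already recorded, and at the existing T2 to T6 contacts.
3. State that between-arm safety comparisons use only items asked identically in all arms, and that findings from the tamoxifen-only item are reported descriptively.
4. Reconcile section 7.4 with section 3 and with the all-arm adverse-event row in the Schedule of Events.
5. Use one attribution term in sections 5.4 and 10.1. For non-serious events, record attribution to each assigned component (tamoxifen, ICR, LI), as section 10.2 already does by treatment for serious events.

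The cost is wording in the protocol and case report forms and a few more minutes per call; no new visit is needed. More grade 1 events will be recorded in the LI arms. The change has to be made before data collection, since unequal questioning cannot be repaired in the analysis.

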## 7.5 Three-month visit

Fasting blood will be drawn for glycemia and blood circulating biomarkers. A stool kit collection will be provided to the participant, to be collected at the final study visit. Date of last menses will be recorded.

Physical exam, vital signs, anthropometric measurement including BIVA, quality of life, food habit and physical activity will be assessed by self-administered questionnaires.

**7.6 Final visit**

Fasting blood drawing for glycemia and circulating biomarkers; stool sample collection. Date of last menses will be recorded

At the final visit, participants will undergo physical exam, vital signs, mammogram if indicate, and anthropometric measurements including BIVA.

The use of concomitant medications, adverse events, quality of life, food habit and physical activity will be assessed. Study agent will be collected and compliance will be evaluated by pills counts and review of agent diary.

## 7.7 Off-Agent Criteria

Participants may interrupt assigned intervention or may stop taking LDT for the following reasons: completed the protocol-prescribed intervention, adverse event or serious adverse event, inadequate agent supply, non-compliance, concomitant medications, medical contraindications, withdrawn consent, positive serum pregnancy test. Participants will continue to be followed, if possible, for safety reasons and in order to collect endpoint data according to the schedule of events. Participants will not be replaced*.*

## 7.8 Off-Study Criteria

Participants may go ‘off-study’ for the following reasons: the protocol intervention and any protocol-required follow-up period is completed, adverse event/serious adverse event, lost to follow-up, non-compliance, concomitant medication, medical contraindication, withdrawn consent, death, determination of ineligibility (including screen failure)*.*

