## 5.5 Adherence/Compliance

To be compliant, a participant has to take ≥ 75% of the scheduled pills and/or follow 75% of the expected days of intermittent caloric restriction as per assigned arm. We propose the use of multiple methods of adherence monitoring: subject self-reporting, diary completion and tablets count.

*Diary completion*: All participants will receive at each visit a calendar to facilitate tracking and recording of protocol treatment (Appendix C). Each participant will be asked to mark or write Yes/No in the corresponding day of the diary. Based on treatment assignment, participants are asked to fill the diary and some additional space will be left for participant’s notes.

A total of 120 pills will be supplied in Arms 1 and 2. Each participant will be asked to return all full and empty blisters.

Should the tablets not be returned, compliance will be calculated from the diary only.

Participants on Arms 2 and 4 will be asked to mark yes/no in the corresponding dates of ICR.

Participants on Arms 3 and 4 will be asked to record the step count number on a weekly basis.

An according-to-protocol subgroup analysis will be restricted to women who are “compliant”, such as participants who have taken ≥ 75% of the pills, for those randomized to tamoxifen and ≥ 75% of the days with the respected caloric restriction, by the reported diary

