# 8. CRITERIA FOR EVALUATION AND ENDPOINT DEFINITION

## 8.1 Primary Endpoint

The main endpoint of the study will be serum concentrations (nmol/L) of SHBG after 6 months of intervention. We expect to obtain a difference of 15 points comparing the two low dose tamoxifen arms with the two other arms that include lifestyle intervention (step counter), with or without intermittent-caloric restriction^57, 58^. The measurement will be centralized at the Division of Cancer Prevention and Genetics at the IEO.

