
The primary analysis will employ an intention-to-treat approach, which includes all participant irrespective of compliance. An according-to-protocol subgroup analysis will be restricted to women who are “compliant”, such as participants who have taken ≥ 75% of the pills, for thus randomized to tamoxifen and ≥ 75% of the days with the respected caloric restriction, by the reported diary.

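### Section 7.8 lets randomised women leave the study for four reasons that section 7.7 treats as ending the intervention only, so 6-month SHBG that the intention-to-treat analysis needs can be lost

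*Protocol*

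**What the plan says.** Protocol section 7.7 (Off-Agent Criteria) gives the reasons for stopping the assigned intervention. Besides completion they are "adverse event or serious adverse event, inadequate agent supply, non-compliance, concomitant medications, medical contraindications, withdrawn consent, positive serum pregnancy test". It then says: "Participants will continue to be followed, if possible, for safety reasons and in order to collect endpoint data according to the schedule of events". It adds: "Participants will not be replaced".

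Section 7.8 (Off-Study Criteria) opens with "Participants may go ‘off-study’ for the following reasons". Besides completion of the intervention and any required follow-up, its list reads "adverse event/serious adverse event, lost to follow-up, non-compliance, concomitant medication, medical contraindication, withdrawn consent, death, determination of ineligibility", and screen failure is named as one form of ineligibility.

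The primary endpoint in section 8.1 is "serum concentrations (nmol/L) of SHBG after 6 months of intervention". Section 12.3 sets the analysis population: "The primary analysis will employ an intention-to-treat approach, which includes all participant irrespective of compliance".

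Section 5.5 defines compliance: "To be compliant, a participant has to take ≥ 75% of the scheduled pills", and/or 75% of the expected days of intermittent caloric restriction (ICR), according to arm. It sets no threshold for the step counter.

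**The concern.** The same event, such as a woman who stops keeping to her assigned intervention, falls under both sections. Under 7.7 she stops the intervention and still comes for her blood draws. Under 7.8 she may leave the study. Two sites could treat identical women differently and both be within protocol.

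The primary analysis is meant to include her regardless of compliance, and she will not be replaced. If 7.8 is applied before month 6, her 6-month SHBG is never measured. Her later quality-of-life, safety and other secondary data go too. A statistical analysis plan can say how missing values are handled, but it cannot recover blood that was not drawn.

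The loss need not be balanced. Compliance is defined only for pills and ICR days, so Arm 3 (lifestyle intervention alone) has no criterion to fail. Tamoxifen side effects arise only in Arms 1 and 2, and section 2.2 reports more menopausal symptoms on low-dose tamoxifen than in the comparison group. The drug combinations named in section 5.3.1 as ones to avoid are tamoxifen interactions. The analysed set could therefore drift towards compliers, mainly on the tamoxifen side.

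**Working it through.** **1. The two lists side by side**

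| Reason | 7.7: stop intervention, follow up if possible | 7.8: may leave study |
|---|---|---|
| Adverse event / SAE | yes | yes |
| Non-compliance | yes | yes |
| Concomitant medication | yes | yes |
| Medical contraindication | yes | yes |
| Withdrawn consent | yes | yes |
| Loss to follow-up, death | no | yes |
| Ineligibility, including screen failure | no | yes |

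Withdrawn consent is also shared, but consent withdrawn for follow-up properly ends follow-up. The conflict concerns the first four rows.

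**2. The plan's own sample size** (section 12.1: difference 15, SD 35, two-sided alpha 5%, 90 per group, 80% power, 10% drop-out, 200 enrolled)

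- Normal approximation: 15 / (35 × √(2/90)) = 2.875; 2.875 − 1.960 = 0.915; power = Φ(0.915) = 82.0%. The t-test gives 81.6%.
- Minimum n for 80% power: 2 × (1.960 + 0.842)² × 35² / 15² = 85.5, so 86 per group; 87 by t-test.
- Enrolment: 180 / (1 − 0.10) = 200.

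The stated figures are reproduced and are slightly conservative.

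**3. Power if more is lost** (t-test, 100 enrolled per pooled group, equal loss, difference still 15)

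| Total loss | n per group | Power |
|---|---|---|
| 10% | 90 | 81.6% |
| 13% | 87 | 80.3% |
| 15% | 85 | 79.3% |
| 20% | 80 | 76.9% |

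If only the tamoxifen group loses more, 80 against 90 gives 79.2% and 75 against 90 gives 77.8%.

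**4. Size of a possible bias.** The protocol gives no off-study or non-compliance rate, so these inputs are assumptions. Let p be the share of tamoxifen women who are non-compliant and r the share of the 15 nmol/L gain that they keep. Assume that compliers gain the full 15, that every non-complier in the tamoxifen arms is excluded, and that losses in the lifestyle arms are unrelated to SHBG.

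- Intention-to-treat difference = 15 × [1 − p(1 − r)].
- Difference after exclusion = 15.
- Overstatement = 1 / [1 − p(1 − r)] − 1.

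| p | r = 0: true difference, overstatement | r = 0.5: true difference, overstatement |
|---|---|---|
| 10% | 13.50, 11% | 14.25, 5% |
| 15% | 12.75, 18% | 13.88, 8% |
| 20% | 12.00, 25% | 13.50, 11% |

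**The case against.** The strongest reply is that the sections can be read together: 7.7 sets continued follow-up as the default, and 7.8 only lists reasons why a woman may nonetheless leave. A reader might infer that 7.8 obliges sites to remove these women. The text does not say that; it is permissive, just as 7.7 is qualified by what is possible. This stands. But discretion leaves the choice to each site, with no rule on which section prevails.

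A reader might also count ineligibility as part of the contradiction. It is not a 7.7 reason. It largely covers screen failures, for whom section 11.2 requires off-study paperwork, and the same section has eligibility confirmed before an arm is generated. Only ineligibility found after randomisation would conflict with intention-to-treat, and 7.8 does not separate the two.

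Other places point towards retention. Section 5.4 speaks of withdrawal from the intervention, not from the study. Non-compliers have a separate according-to-protocol analysis, which presupposes that they remain in the main one. The specimen table in section 9.4 foresees serum at study cessation, so not every value would be missing. That value is not the 6-month one, however. Pill counts take place only when blisters are returned at month 6 (section 7.1), at the same visit as the primary blood draw, so early removal for missed pills would have to rest on the diary or self-report. This makes the tamoxifen non-compliance route less likely without closing it.

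On direction, a reader might take overstatement of the tamoxifen effect as certain. ICR is in Arm 2 and Arm 4, one on each side of the primary contrast. Since section 2 expects caloric restriction to raise SHBG, losing ICR non-compliers from Arm 4 could raise the lifestyle mean and shrink the difference. On size, section 2.3 reports that lower tamoxifen doses still modulate SHBG, so zero gain in non-compliers is an extreme case; hence the range down to half the gain lost.

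**Conclusion.** The overlap is real: four reasons sit in both lists with different consequences, and no text settles which applies. Applying 7.8 to a randomised woman can lose a primary endpoint value that section 12.3 requires. Loss may differ by arm, and overstatement of the tamoxifen effect is the likely direction, though not a certain one. Under the stated assumptions the overstatement runs from about 5% to 25%; the protocol supplies neither the non-compliance rate nor the gain kept.

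Bias matters more than power. The design holds 80% up to about 13% total loss and has about 77% at 20%. The documents do not support a claim that the sample size is wrong or that 7.8 mandates removal.

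**What to change.** Reconcile 7.7 and 7.8. For randomised women:

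- State that adverse event/SAE, non-compliance, concomitant medication and medical contraindication can end the intervention but do not end follow-up.
- Limit off-study reasons to completion, withdrawal of consent to follow-up, loss to follow-up and death.
- Confine determination of ineligibility to screen failure before randomisation.
- State that stopping the intervention does not cancel the scheduled 3- and 6-month blood draws and questionnaires.

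The rules for stopping treatment stay unchanged. The cost is a short amendment, a reminder to sites, and keeping visits that are already scheduled for women who stop the intervention.
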